## Abstract

**Background:**

Antibiotic associated diarrhoea complicates 5–39% of courses of antibiotic treatment. Major risk factors are increased age and admission to hospital. Of particular importance is *C. difficile* associated diarrhoea which occurs in about 4% of antibiotic courses and may result in severe illness, death and high healthcare costs. The emergence of the more virulent 027 strain of *C. difficile* has further heightened concerns. Probiotics may prevent antibiotic associated diarrhoea by several mechanisms including colonization resistance through maintaining a healthy gut flora.

**Methods:**

This study aims to test the hypothesis that administration of a probiotic comprising two strains of lactobacilli and two strains of bifidobacteria alongside antibiotic treatment prevents antibiotic associated diarrhoea. We have designed a prospective, parallel group trial where people aged 65 years or more admitted to hospital and receiving one or more antibiotics are randomly allocated to receive either one capsule of the probiotic or a matching placebo daily for 21 days. The primary outcomes are the frequency of antibiotic associated and *C. difficile* diarrhoea during 8–12 weeks follow-up. To directly inform routine clinical practice, we will recruit a sufficient number of patients to demonstrate a 50% reduction in the frequency of *C. difficile* diarrhoea with a power of 80%. To maximize the generalizability of our findings and in view of the well-established safety record of probiotics, we will recruit a broad range of medical and surgical in-patients from two different health regions within the UK.

**Discussion:**

Antibiotic associated diarrhoea constitutes a significant health burden. In particular, current measures to prevent and control *C. difficile* diarrhoea are expensive and disrupt clinical care. This trial may have considerable significance for the prevention of antibiotic associated diarrhoea in hospitals.

**Trial registration:**

International Standard Randomised Controlled Trial Number Register ISRCTN70017204.

## Background

Antibiotic-associated diarrhoea (AAD) is diarrhoea that occurs in association with antibiotic treatment and without an alternative cause [1]. It is estimated to occur in 5 – 39% of people taking antibiotics during or up to 12 weeks after treatment [2]. AAD varies markedly in severity from mild diarrhoea to severe diarrhoea as part of a life-threatening illness caused by the anaerobic bacterium *Clostridium difficile* (*Clostridium difficile* associated diarrhoea*;* CDAD) which accounts for 15–39% of cases of AAD [3]. A particular concern is the emergence of the hypervirulent ribotype 027 strain of *C. difficile* documented in Canada, USA and Europe [4]. Even mild diarrhoea may cause significant morbidity and prolong hospital stay. The annual healthcare cost of CDAD in the USA was estimated to be more than $3 billion [5,6].

Host risk factors for AAD include advanced age, immune suppression, gastrointestinal disease or previous gastrointestinal surgery and severe co-morbidity [2,3,7]. AAD can complicate treatment with any antibiotic but broad spectrum antibiotics (clindamycin, cephalosporins, β-lactamase resistant penicillins, quinolones), antibiotic combinations and repeated or long treatment courses are associated with the greatest risk of AAD [2,7]. Other environmental factors include admission to hospital, longer duration of stay and use of naso-gastric tubes [8]. Suppression of gastric acid may also be an additional risk factor for CDAD in both hospital inpatients [9] and people in the community [10].

Antibiotics may result in diarrhoea through several mechanisms. Antibiotic disruption of the commensal gut microorganisms results in osmotic or secretory diarrhoea from changes in carbohydrate, short chain fatty acid and bile acid metabolism and impaired colonization resistance allowing a competitive growth advantage to diarrhoeagenic organisms [11-13].

Given the frequency and potential severity of CDAD, extensive and costly strategies for the prevention of AAD have become an established part of hospital in-patient management. These include strict limitations on the use of antibiotics, hand washing, isolation of diarrhoea patients and decontamination of the environment [14]. However, despite these efforts, the heat- and drying-resistant spores of *C. difficile* persist in the modern hospital environment [15,16].

In view of the mechanisms underlying AAD, probiotics offer a potential means of prevention. Probiotics are defined as live microbial organisms which, when administered in adequate numbers, are beneficial to health [17]. In a recent meta-analysis, McFarland [18] pooled data from 25 RCTs (total of 2,810 adults and children) and reported a reduced relative risk of AAD in participants receiving a probiotic (0.43; 95% CI 0.31 – 0.58). Trials of many different single strains of probiotic bacteria, the yeast *Saccharomyces boulardii (S. boulardii*)*,* probiotic mixtures and probiotic and prebiotic mixtures were included in this analysis. Dosage (number of organisms) also varied markedly between studies. In sub-group analyses, factors associated with greater efficacy in preventing AAD were use of *S. boulardii* or *Lactobacillus rhamnosus (L. rhamnosus) GG*, mixtures of probiotics and preparations with high numbers of organisms.

Members of our research group [19] assessed the effect of a combination of *L. acidophilus* and *B. bifidum* on CDAD in a pilot study in elderly patients receiving antibiotics. Overall, 30/138 (22%) patients developed diarrhoea with 5/69 in the placebo group and 2/69 in the probiotic group testing positive for *C. difficile* toxin. In this small study, the main effect of the intervention appeared to be neutralisation of the toxin rather than prevention of colonization with *C. difficile*. The meta-analysis by McFarland [18] included 5 studies, in addition to our study, but all of these were treatment trials of patients with established or recurrent CDAD. When designing our study, apart from a small trial with few CDAD cases [20], we were not aware of other studies that had assessed probiotics in the primary prevention of CDAD in hospitalized adults. Since then, reports of trials have been consistent with the prevention of CDAD by lactobacilli and bifidobacteria although relatively small numbers of participants were recruited [21,22].

Probiotics were classified by the US Food and Drug Administration in 2002 (notice GRN 000049) as “generally regarded as safe”. Reported adverse events in research studies were mild but occurred with *S. boulardii* (constipation, increased thirst) and *L. rhamnosus* GG (bloating, gas) [18]. Probiotics have been administered without adverse effects to vulnerable groups such as children and adults with HIV infection and preterm infants [23]. However, an expert group in the USA concluded recently that although the available evidence from randomised trials did not indicate a widespread risk of adverse events, researchers should monitor and quantify adverse events in future probiotic intervention studies [24].

In summary, a variety of probiotics appear to reduce the risk of AAD. However, the large number of different probiotics and different regimens that have been evaluated compromises the development of clinical practice guidelines. Also, many trials have included only a small number of participants, trial methods have often been poor, the period of follow-up limited and the quality control of the probiotic interventions has been inadequate [25]. There are insufficient data to assess the effectiveness of probiotics in the prevention of CDAD.

## Presentation of the hypothesis

In older people admitted to hospital and treated with one or more antibiotics, administration of a multi-strain probiotic would reduce the frequency of AAD and CDAD.

## Testing the hypothesis

This study is a double-blind, randomized, parallel group, placebo-controlled trial. We plan to recruit patients with a wide range and severity of illness from as many wards as possible in 5 secondary care hospitals from 2 geographically distant UK health authorities, in order to be confident that our findings are applicable to a diverse range of older patients admitted to National Health Service (NHS) hospitals and similar institutions. Planned recruitment sites in the Abertawe Bro Morgannwg University Health Board (ABMUHB), South West Wales are Singleton and Morriston hospitals (total 1450 beds), and in the County Durham and Darlington Foundation NHS Trust (CDDFT), University Hospital of North Durham, Bishop Auckland General Hospital and Darlington Memorial Hospital (1353 beds). In 2005/6 (12 months), 26,692 people aged ≥65 years were admitted in Swansea and 21,676 in CDDFT and approximately one third received antibiotics.

Inclusion and exclusion criteria are shown in Table 1. Exclusion criteria will be limited to possible contraindications to probiotics identified in previous studies and case reports [23]. In particular, following the findings of the PROPATRIA trial [26], we will exclude patients with severe illness requiring high dependency or intensive care (but not planned admission to these facilities for observation only), acute pancreatitis, any known abnormality or disease compromising intestinal blood supply, and those with a jejunal tube *in situ* or receiving jejunal feeds .

**Table 1 T1:** Criteria for participant inclusion and exclusion

	· people aged ≥65 years and admitted to hospital
**Inclusion criteria**	· exposed to one or more antibiotics within the last 7 days or are about to start antibiotic treatment
	· consultant approval to invite patient to join the study
	· diarrhoea present^1^
	· immunocompromise^2^
	· severe illness requiring high dependency or intensive care^3^
	· prosthetic heart valve
	· *C. difficile* in past 3 months
**Exclusion criteria**	· active inflammatory bowel disease^4^
	· suspected acute pancreatitis^5^
	· known compromised gut blood supply^6^
	· jejunal tube *in situ* or receiving jejunal feeds
	· previous adverse reaction to probiotics
	· unwilling to discontinue exiting use of probiotics

^1^Defined as 3 or more watery or loose stools (Bristol Stool Form Scale types 5–7) in a 24 h period. ^2^Sufficient to require isolation and barrier nursing. ^3^Planned admission to these facilities for observation only is not an exclusion criteria. ^4^Required specific treatment in past 12 months. ^5^Abdominal pain with serum amylase/lipase ≫ ×3 institutional upper limit of normal. ^6^Abnormality or disease of mesenteric vessels or coeliac axis.

The investigational medicinal products (IMPs) will be discontinued and participants withdrawn from the study if they develop pancreatitis or severe illness that requires high dependency or intensive care. However, these participants will be included in intention-to-treat analysis.

The flow chart regarding screening, recruiting and following-up participants is shown in Figure 1. A research nurse will take signed, informed consent according to standard guidelines [27]. It is expected that some potential participants will not be able to give informed consent because of impaired mental capacity. Assent will be sought from next of kin, other relatives or carers in line with Article 5 of the EU Directive 2001/20/EC (Clinical Trials on incapacitated adults not able to give informed legal consent). The consent form will be held in the investigator file, with copies filed in the hospital notes and given to the participant. A sticker will be placed on the hospital notes and the patient’s General Practitioner informed by letter. The reasons for declining to participate, if provided, will be recorded.

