### Follow-up

Research nurses will review participants daily during admission to determine the onset, frequency and duration of any diarrhoea and ask about gastrointestinal symptoms (abdominal pain, bloating, flatus, nausea), acceptability and adverse effects of the interventions. After discharge, follow-up will be weekly by telephone call, postal questionnaire or home visit as appropriate. Participants will be provided with contact details for ready telephone access to research staff to notify the onset of diarrhoea or adverse events. All participants will be followed-up for 8 weeks after completing antibiotic treatment to a maximum of 12 weeks from recruitment for those on longer antibiotic courses.

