### Outcome measures

The two outcomes used to generate the sample size, AAD and CDAD, have been identified as co-primary outcomes (Table 3). Diarrhoea is defined as 3 or more loose stools in a 24 h period. We will use the Bristol Stool Form Scale [29] to assist participants in describing stool consistency; types 5-7 will be consistent with diarrhoea.

**Table 3 T3:** Outcome measures

**Primary outcomes**	1. the occurrence of AAD
	2. the occurrence of CDAD
	1. severity^1^ and duration of AAD
	2. severity^1,2^ and duration of CDAD and incidence of recurrence within the 8-12 weeks follow-up period
	3. abdominal symptoms (abdominal pain, bloating, flatus, nausea)
**Secondary outcomes**	4. well-being and quality of life assessed using the generic measures EQ-5D and the York SF12 (Iglesias 2001) at recruitment and 4 and 8 weeks
	5. duration of hospital stay
	6. serious adverse effects
	7. acceptability of the probiotic preparation
	8. viability of the probiotic at point of administration
	9. cost-effectiveness

^1^Frequency and consistency of stools. ^2^Additional information extracted from the clinical records (*e.g.* laboratory parameters, findings at sigmoidoscopy, pseudomembraneous colitis, colectomy, death).

All participants who develop diarrhoea during the study period will be asked to provide a stool sample and this will be collected during a home visit if required. The cause of diarrhoea will be determined by NHS laboratories according to their usual practice. Stools will be analysed for diarrhoeal pathogens (bacterial culture for *Salmonella* sp, *Shigella* sp, Campylobacter, *E. Coli* 0157; wet film for ova, cysts and parasites) and for *C. difficile* toxins. In ABMUHB, *C. difficile* will be identified by an in-house culture assay with further analysis by Meridian Premier Toxin A + B Enzyme Immunoassay (Meridian Bioscience Europe Inc., Cincinnati, USA) if required. In CDDFT, toxins are identified using the mini VIDAS system (C. diff Quik Check, Techlab, Blacksburg, U.S.A.). If a cause of the diarrhoea is not identified, a further stool sample will be collected and tested 2 days later.

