For the primary outcome measures, AAD is defined as diarrhoea without pathogens detected on routine laboratory analysis, negative for *C. difficile* toxin and without alternative cause (e.g. laxative treatment). CDAD is defined as diarrhoea with stools positive for *C. difficile* A or B toxin. For quality control purposes, *C. difficile* culture and confirmation by immunoassay will be undertaken in 1 in 5 *C. difficile* toxin positive stool samples collected in Swansea. In view of the known inadequacies of current methods for the laboratory diagnosis of *C. difficile *[30], we will also save stool samples at −20°C from participants with diarrhoea for further testing for the glutamate dehydrogenase antigen and also lactoferrin (IBD scan and C. diff Quik Chek Complete; Alere Limited, Stockport, UK). This may result in the diagnosis of CDAD that was not detected by routine methods.

Participants who develop severe diarrhoea will be investigated and managed according to the current practice of their clinicians. We will extract information from the clinical records (*e.g.* laboratory parameters, findings at sigmoidoscopy, colectomy) to classify the severity of CDAD. At the end of follow-up, participants will be classified as either developing AAD, CDAD, another cause of diarrhoea (*e.g.* norovirus) or no diarrhoea. Other endpoints have been listed as secondary outcomes (Table 3).

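### The rule for pancreatitis or HDU/ICU-level illness ties stopping the capsules to leaving the study, and is not reconciled with intention-to-treat inclusion or with follow-up of all participants

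*Protocol article*

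**What the plan says.** In the text after Table 1 (Testing the hypothesis), the article attaches two actions to the onset of pancreatitis or of illness at high dependency or intensive care level. The investigational product is stopped, and the participant leaves the trial: "participants withdrawn from the study if they develop pancreatitis or severe illness that requires high dependency or intensive care". The next sentence qualifies this: "However, these participants will be included in intention-to-treat analysis".

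The Follow-up section sets one schedule for everyone: "All participants will be followed-up for 8 weeks after completing antibiotic treatment to a maximum of 12 weeks from recruitment". In hospital, detection of the primary outcomes depends on active review: "Research nurses will review participants daily during admission to determine the onset, frequency and duration of any diarrhoea". After discharge, contact is weekly. Withdrawn participants are not mentioned.

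Outcome measures requires a stool sample from anyone with diarrhoea, tested in NHS laboratories under their usual practice. It closes with a classification: "At the end of follow-up, participants will be classified as either developing AAD, CDAD, another cause of diarrhoea", or no diarrhoea. The footnote to Table 3 lists information to be taken from clinical records on CDAD severity, including "pseudomembraneous colitis, colectomy, death".

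**The concern.** Stopping a treatment and stopping observation are different acts, and the sentence joins them. If the capsules alone were meant, the first clause would have been enough. A site team that applied the second clause as written would have reason to end daily review and weekly contact.

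Inclusion in an intention-to-treat analysis does not repair that. Such an analysis needs an outcome for each participant as well as a place in the denominator. Both co-primary outcomes need someone to notice diarrhoea, and CDAD also needs a toxin test. With no class for unknown, a withdrawn participant without recorded diarrhoea could be counted by default as having none.

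The loss would not be random. The trigger arises after randomisation and marks severe illness. The Background describes CDAD as part of a life-threatening illness at its worst, and lists severe co-morbidity and longer stay among the risk factors for AAD. The safety section lists pancreatitis and multi-organ failure as suspected reactions, so the plan itself treats a product effect on the trigger as conceivable. Later CDAD recurrence and severity, and length of stay, would be exposed to the same gap.

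**Working it through.** **1. The passages side by side**

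| Question | Testing the hypothesis | Follow-up | Outcome measures |
|---|---|---|---|
| Is the product stopped? | Yes | – | – |
| Is the participant still in the study? | No | Yes, no exception | Everyone is classified |
| Is the participant analysed? | Yes, intention-to-treat | – | Four classes, none for unknown |
| Does outcome collection continue? | Not stated | Yes, if it applies to all | Not stated for withdrawn participants |

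The first two columns agree only if withdrawal means withdrawal from the product. The text says from the study.

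**2. The plan's own sample size**

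Inputs from Sample size and recruitment: CDAD 4% against 2%, 5% significance (two-sided), 80% power, 1:1 allocation.

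- Uncorrected: n = [1.960·√(2·0.03·0.97) + 0.8416·√(0.04·0.96 + 0.02·0.98)]² / 0.02² = 1,140.8, so 1,141 per arm.
- Continuity-corrected: (1,140.8/4)·[1 + √(1 + 4/(1,140.8·0.02))]² = 1,238.8, so 1,239 per arm and 2,478 in total. This matches the article exactly.
- Expected CDAD cases at the design rates: 1,239 × (0.04 + 0.02) = 74.3.

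**3. Illustration of missed events (assumed shares)**

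The article gives neither a withdrawal rate nor a share of CDAD arising after withdrawal. Assume a share f of CDAD events in both arms is missed and scored as no event. The rates become 0.04(1−f) and 0.02(1−f), and

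power = Φ{ [p₁ − p₂ − 1/n − 1.960·√(2p̄(1−p̄)/n)] / √[(p₁(1−p₁) + p₂(1−p₂))/n] }.

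| f | Cases missed of 74.3 | n = 1,239, corrected | n = 1,239, uncorrected | n = 1,487, corrected |
|---|---|---|---|---|
| 0 | 0 | 80.0% | 83.1% | 87.1% |
| 5% | 3.7 | 77.7% | 81.2% | 85.2% |
| 10% | 7.4 | 75.2% | 79.0% | 83.1% |
| 20% | 14.9 | 69.5% | 74.0% | 78.0% |

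The 1,487 per arm is the planned recruitment of 2,974 divided by 2. It is the relevant denominator if withdrawn participants stay in the analysis and nobody else is lost. The article expects other losses (10% drop-outs and 10% deaths), so that column is optimistic.

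Equal proportional loss in both arms leaves the risk ratio at 0.5. The cost is fewer events and a smaller risk difference.

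**4. Illustration of unequal withdrawal (assumed rates)**

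With no true effect, and with every withdrawn participant scored as no event, the apparent risk ratio is (1 − w probiotic)/(1 − w placebo):

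- 5% against 2%: 0.95/0.98 = 0.97.
- 10% against 5%: 0.90/0.95 = 0.95.

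These are upper-end distortions for those rates at average CDAD risk, because events before withdrawal would still be observed.

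**The case against.** A reader might infer that these participants enter the analysis without ascertained outcomes, and that a genuine intention-to-treat analysis is therefore impossible. The documents do not support either statement. The article never says that follow-up stops. The sentence that keeps these participants in the analysis, together with a follow-up rule that has no exception, also allows the reading that only the product is withdrawn. The full protocol may define the term, and the flow chart is not shown.

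Other points also stand:

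- Events before the trigger are observed on either reading. CDAD severe enough to lead to intensive care would usually have begun before it.
- NHS laboratories test stools under usual practice, and clinical records are used for CDAD severity. Both sources can exist without research-nurse contact.
- Pancreatitis and multi-organ failure go immediately to the Independent Safety Monitor, and serious adverse events are reviewed regularly. It cannot be said that safety events are lost.
- Differential withdrawal by arm is a possibility in this double-blind trial, and the article offers no evidence for it.
- The power figures rest on assumed shares, and planned recruitment gives some margin.

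What does not stand is the suggestion that nothing needs changing. The sentence orders withdrawal from the study as a separate act from stopping the product. Extraction from records is described for grading CDAD severity, and the article does not offer it as a way to detect new diarrhoea. An analysis plan may say how missing outcomes are handled, but it cannot recover outcomes that a conduct rule stopped collecting.

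**Conclusion.** The point holds as an unreconciled conduct rule. One section withdraws a severity-selected group from the study and analyses them as randomised; another follows everyone for 8 to 12 weeks. On the literal reading, AAD and CDAD arising after withdrawal could go undetected and be counted as no diarrhoea. On the milder reading nothing is lost, but the text does not say so.

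The size of any effect cannot be derived from the document. The power range of 77.7% to 69.5% at 1,239 per arm (85.2% to 78.0% at 1,487) assumes that 5% to 20% of CDAD events are missed equally in both arms. It shows direction and does not demonstrate a shortfall. The apparent risk ratios of 0.97 and 0.95 under no effect likewise depend on assumed withdrawal rates. The clinical rule for stopping the product is not in question.

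**What to change.** Reconcile the text after Table 1 with the Follow-up section. Leave the rule for discontinuing the product unchanged. Replace the words that withdraw these participants from the study with a statement that outcome follow-up (AAD, CDAD, death, serious adverse events and length of stay) continues to the planned end, through ward review, clinical records and NHS laboratory reports. Reserve withdrawal from the study for withdrawal of consent or assent.

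The cost is a one-sentence amendment and a few more follow-up contacts by research nurses who already visit these hospitals. It should be made while the trial is running, since outcomes not collected at the time may not be recoverable later.
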